### Study status

The study protocol was reviewed and approved by the Institutional Review Board of SAJIDA Foundation on 8^th^ February 2024 (reference number 2024–005-SFIRB). The research team had conducted one stakeholder meeting with formal caregivers and intends to conduct at least another one with family caregivers of PWD to discuss the adapted iSupport manual and pre-test the tools for the feasibility study. Participant recruitment and data collection have not begun yet and is planned to begin in the last week of July 2024. The recruitment process of family caregivers is currently being discussed with relevant organizations and healthcare professionals.

## Discussion

For this study, the WHO’s iSupport manual has been adapted to the Bangladeshi context. This study plans to assess the feasibility and effectiveness of the Bangla iSupport manual in improving dementia knowledge and caregiving skills among family and formal caregivers in Dhaka, Bangladesh. This adaptation is the first Bangladeshi adaptation of the WHO iSupport manual and is anticipated to be among the few caregiving support resources in Bangladesh, that is backed by well-established therapeutic techniques.

Currently, there is a lack of policy on dementia care and guidelines on practice in Bangladesh. Findings of this pioneering study will help structure competence-building for both family and formal caregivers in their role for caring for PWD. This is one of the few studies, if not the first one in Bangladesh, which will help create a knowledge base on care strategies for a PWD living at home and self-care strategies for caregivers themselves.

This research aims to contribute significantly to the limited literature on dementia care in Bangladesh and limited formal training and support services for caregivers. We anticipate that participation in this study will enhance knowledge on dementia among participating caregivers. This in turn may help caregivers better manage PWD [18,19]. This study, however, will not assess the impact of caregivers utilizing the iSupport manual on PWD. Moreover, we anticipate reduced stress and improved mental health outcomes in family caregivers to PWD. This is particularly important in Bangladesh, where mental health support is limited [53].

Through this research, a web-platform and caregiving content will be developed for Bangladeshi Bangla-language speakers in Bangladesh. The research team aims to prepare manuscripts detailing the adaptation process of the iSupport manual, and findings and implications of the intervention. The manuscripts will be submitted to international journals specializing in dementia care, healthcare and caregiver support. The research team also plans to present findings in relevant conferences and seminars. Additionally, the findings of this study and evidence-based recommendations will be communicated with healthcare providers and other organizations working with dementia care through stakeholder meetings and policy briefings.

This feasibility study will provide insights into the feasibility of implementing the iSupport manual in Bangladesh, where caregiving is largely informal, with most PWD receiving care from a family member with little knowledge or paid individual with limited educational qualifications. The findings could inform future adaptations of iSupport for formal caregivers. Lessons learned from the adaptation process, combined with the feedback from stakeholders and participants, will help refine the content and delivery modalities (i.e., online, paper-based, or in-person training) to increase cultural relevance, ease of understanding, and accessibility in resource-constrained settings. These insights will help lay the groundwork for broader trials and scale-up efforts in Bangladesh and other LMICs.

### Limitations

The study will employ a non-randomized design and purposive sampling to recruit participants. Furthermore, all formal caregivers included in the study will be exclusively selected from a single agency. These methodological choices may introduce selection bias and limit the generalizability of findings. The absence of a control group, due to financial and logistical constraints, will limit the ability to evaluate the effectiveness of the iSupport intervention in achieving the secondary objectives among family caregivers. Moreover, given the iSupport intervention will be online for most participants, internet connectivity and digital literacy may pose as a barrier to proper access and adherence to the intervention. If this occurs, we will be unable to measure the potential effectiveness of the iSupport manual. Use of the printed manual also presents potential challenges, such as the risk of participants photocopying or retaining the manual, which could compromise the accurate assessment of knowledge retention during the follow-up survey.

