**Fig 3 pone.0326207.g003:**
[figure not shown]
Overview of the iSupport modules and lessons. Adapted from the WHO’s iSupport manual [22].

For this research, the Bangladeshi adaptation of the iSupport manual will be uploaded online, where participants must log in using unique log in credentials provided by the research team. The platform will allow participants to access and navigate modules in any order, add and save personal notes on each page, and complete quizzes at the end of each section. Like the original manual, the answers will be available at the end of each section. The research team can track participants’ progress and access saved notes through website analytics.

Both family and formal caregivers will be given access to the website for two months, subsequent to taking part in the baseline survey. Although the iSupport manual was initially designed as a web-based self-help tool, the WHO also states it can be printed and used offline, allowing easy access for users with poor internet connection, no smart phones or other mobile devices, and no access to computers [22]. Therefore, formal caregivers recruited in this study will also have access to printed versions of the manual as they are likely to have limited access to internet or they may not have compatible devices or devices with large enough screens to view the manual. Moreover, formal caregivers will receive face-to-face training on how to use the iSupport manual prior to obtaining access to the manual. Study participants are sent a weekly reminder of their access duration and to encourage engagement with the iSupport manual. Access to, both, online and printed versions will be restricted by disabling online access and taking back the printed manual before their end-line survey.

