### Study instruments

Quantitative and qualitative data collection tools will be used to assess the primary and secondary objectives of this study. Bangla version of all data collection instruments will be used for this feasibility study.

Since the primary objective of this feasibility study is to assess the knowledge on dementia and dementia care, the Dementia Knowledge Assessment Scale (DKAS) [39] will be used to measure the change in knowledge among both family and formal caregivers. Caregiving skills will be assessed as one of the secondary objectives for family caregivers. For this purpose, a Caregiver Competency (CC) instrument has been developed by the research team upon reviewing relevant literature and existing tools, and the contents of the iSupport manual.

The level of burden, depression and anxiety experienced by family caregivers will be assessed as secondary objectives as well. This will be done using the Modified Caregiver Strain Index (MCSI) [40], Center for Epidemiological Studies of Depression Short Form (CES-D-10) [41] and the General Anxiety Disorder – 7 (GAD-7) [42]. This study will also assess quality of life of family caregivers by using the care-related Quality of Life Instrument (CarerQoL) [43]. Additionally, family caregivers’ relationship with PWD will be assessed using the Quality of Carer-Patient Relationship (QCPR) [44]. It is important to note, while the QCPR instrument is designed to be asked to, both, the caregiver and care-recipient, in this study only the caregivers’ response will be recorded. The study instruments mentioned will be administered in Bangla. All tools except GAD-7 and CESD-10 were translated by the research team and pre-tested with caregivers. The Bangla GAD-7 [45,46] and CESD-10 [47] were previously validated in studies conducted in Bangladesh.

Semi-structured interview guidelines will be used to conduct qualitative interviews with the family and formal caregivers. In these qualitative interviews, participants’ experiences with iSupport, the benefits they derived from it, the challenges they faced, and potential suggestions to address those challenges will be discussed.

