### Data collection plan

Once the iSupport manual has been fully translated, reviewed, and face-validated through stakeholder workshops, participant recruitment and data collection will commence. Trained data collectors will conduct the data collection. The data collectors will undergo vigorous training on the study instruments prior to data collection. Data collection will begin with a baseline survey, after which participants will gain access to the manual for two months. At the end of the two months, an end-line survey will be conducted. Following the end-line survey, qualitative interviews to explore the experiences, facilitators, and barriers of using iSupport will be conducted. Finally, a follow-up survey will be conducted to test the retention of knowledge on dementia after three months of the end-line survey. Figs 1 and 2 show the adaptation, participant recruitment and data collection timeline of family and formal caregivers.

The DKAS [39] will be used at baseline and end-line to assess the primary objective for both family and formal caregivers. The DKAS will also be used three months after the end-line to assess the retention of knowledge among both caregiver groups. The CC, MCSI [40], CES-D-10 [41], GAD-7 [42], CarerQoL [43] and QCPR [44] will be administered at baseline and end-line only to assess the secondary objectives relating to family caregivers in this study. All data collection tools used will be used to record caregivers’ responses only and will not involve the PWD. The timeline for administering each tool is shown in Fig 4.

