**Fig 4 pone.0326207.g004:**
[figure not shown]
Data collection and tool administration timeline.

In addition, baseline data such as gender, age, participants’ socio-demographic, economic features, and experience of caregiving will be collected. Website analytics will be collected to assess participants’ adherence to the program. Combined with website analytics, a self-reported adherence module at end-line will be used to assess adherence. Moreover, a minimum of 15 individual qualitative interviews with family caregivers and four FGDs with formal caregivers will be conducted after the end-line. Additional interviews and FGDs may need to be conducted until data saturation is reached. Participants with varied degrees of adherence will be invited to participate in the interviews and FGDs.

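### No use of iSupport material is described as measured after end-line, so among formal caregivers a kept manual could pass for retained knowledge; the limitations also omit that interviews and FGDs precede the three-month DKAS (minor)

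*Protocol article*

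**What the plan says.** All references are to the protocol article.

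- **Purpose of the follow-up.** Under Data collection plan, "a follow-up survey will be conducted to test the retention of knowledge on dementia after three months of the end-line survey". The DKAS is named for this in both caregiver groups; Study design gives the same purpose and timing.
- **Control of access.** Under The iSupport intervention: "Access to, both, online and printed versions will be restricted by disabling online access and taking back the printed manual before their end-line survey". Printed copies are described for formal caregivers only; family caregivers must have internet access to be eligible.
- **Disclosed residual risk.** Under Limitations, use of the printed manual carries "the risk of participants photocopying or retaining the manual, which could compromise the accurate assessment of knowledge retention during the follow-up survey".
- **Measurement of use.** Under Data collection plan, website analytics are combined with a self-report: "a self-reported adherence module at end-line will be used to assess adherence". No measure of use after end-line is described.
- **Order of the qualitative work.** Under Data collection plan: "Following the end-line survey, qualitative interviews to explore the experiences, facilitators, and barriers of using iSupport will be conducted". The follow-up survey is then listed as the final step. On numbers, "a minimum of 15 individual qualitative interviews with family caregivers and four FGDs with formal caregivers will be conducted after the end-line", with more possible until saturation. On selection, "Participants with varied degrees of adherence will be invited to participate in the interviews and FGDs".
- **Content of the qualitative work.** Under Study instruments: "participants’ experiences with iSupport, the benefits they derived from it, the challenges they faced, and potential suggestions to address those challenges will be discussed".

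**The concern.** A retention score is meant to show what people still know after exposure has stopped. That reading needs exposure to have stopped, or at least a record of who went on using the material.

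The protocol tries to stop exposure and admits that this may fail for printed manuals. It describes nothing that would reveal a failure. There is no control group to show the follow-up score expected without continued use. A formal caregiver who photocopied the manual and one who remembers its content would look the same at three months. Later analysis cannot repair this, because the data would not exist.

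The second issue is smaller. Some participants spend time discussing iSupport with the research team between end-line and the retention test. That may prompt recall or interest. The limitations discuss the kept manual as a threat to retention but do not mention this contact.

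What is at stake is the interpretation of the retention result. The baseline to end-line comparison, on which the primary question and the sample size rest, is complete before either route opens.

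**Working it through.** **1. The plan's own figures, used here as denominators.** Formula from Sample size: n = ((z₀.₉₇₅ + z₀.₈₀) / (μ_d/σ_d))², with (1.960 + 0.842)² = 7.849.

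- Family: gain 15.0, SD 9.0 × 3 = 27.0. n = 7.849 × (27.0/15.0)² = 25.43, so 26, as stated.
- Formal: gain 9.9, SD 8.7 × 2 = 17.4. n = 7.849 × (17.4/9.9)² = 24.25, so 25, against 26 stated. The difference of one has no bearing here.
- 40% attrition: 26/0.60 = 43.3, so 44, as stated. Expected completers are about 26 family caregivers and 132 × 0.60 = 79 formal caregivers.

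**2. Could use after end-line be seen in the data described?**

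| Source | Covers use after end-line? |
|---|---|
| Website analytics | No: online access is already closed, and logs never capture paper use |
| Self-reported adherence module | No: given at end-line |
| Three-month survey | Only the DKAS is named for it |
| Comparison group | None |

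**3. Size of the kept-manual route (formal caregivers; illustration on assumed inputs).** Let r be the share of the gain retained without the manual and p the share of formal caregivers still using it, and suppose users keep the full gain. Apparent retention = r(1 − p) + p. Assume r = 0.5 and take the 9.9-point gain from Sample size, so true retention is 5.0 points.

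- p = 0.10: 0.5 × 0.90 + 0.10 = 0.55, or 5.4 points.
- p = 0.30: 0.5 × 0.70 + 0.30 = 0.65, or 6.4 points.

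The overstatement is p(1 − r) × 9.9 = 0.5 to 1.5 points. The documents give neither r nor p.

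**4. How many people the interviews and FGDs touch.**

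- Family: 15/44 = 34% of those enrolled, or 15/26 = 58% of expected completers if every interviewee completes.
- Formal: FGD size is not stated. Assuming 6 to 10 per group, four groups hold 24 to 40 people. That is 24/132 = 18% to 40/132 = 30% of those enrolled, or 24/79 = 30% to 40/79 = 51% of expected completers.

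**5. What that could do to the mean.** Shift = share involved × effect per participant. For an assumed effect of 1 to 5 DKAS points:

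- Family: 0.34 × 1 = 0.3 to 0.577 × 5 = 2.9 points, against a planned gain of 15.0.
- Formal: 0.18 × 1 = 0.2 to 0.506 × 5 = 2.5 points, against 9.9.

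The effect could also be zero.

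**6. What a comparison of participants and non-participants could show.** Family, 15 interviewed and 26 − 15 = 11 not: SE = SD × √(1/15 + 1/11). With SD 9 the SE is 3.57, and the difference detectable at 80% power is 2.802 × 3.57 = 10.0 points. With SD 27 it is 30.0. Formal, 24 against 55 completers: 6.0 points with SD 8.7, and 11.9 with SD 17.4. These SDs are for the baseline to end-line change and stand in for the unknown SD of the later change. The comparison would not settle a small effect, and it is confounded because invitations depend on adherence.

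**The case against.** The strongest reply is that the authors have dealt with the manuals openly: they withdraw both formats before end-line, then name the remaining risk and its consequence. This stands. A reader might infer that the plan ignores kept manuals; it does not. What is absent from the description is a measurement that would show how far the risk materialised.

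Second, the printed-manual route does not extend to family caregivers. This also stands, and the point is limited accordingly.

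Third, a reader might take the interviews and FGDs for a refresher session that raises the DKAS. The documents do not support this. The stated topics are experience, benefits, challenges and suggestions; nothing describes teaching, showing the manual or going over DKAS answers. Direction and size of any effect are unknown. Attendance can also be linked through the unique participant ID described under Data management, so this route can be examined without new data.

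Fourth, the article does not say that the three-month survey contains only the DKAS, and the tool schedule (Fig 4) is not shown. This stands as a caveat: if exposure items already exist in the full questionnaire, that part of the point falls away. Nor does the article say that all participants will be pooled in one retention estimate, so that should not be assumed.

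Finally, retention appears neither under Objectives nor under Research questions. That bears on the weight of the point, not on whether it is true.

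**Conclusion.** The point holds in a limited form. As described, the plan would yield a retention score for formal caregivers that continued use of a copied or kept manual could inflate, with no data to show whether it had. In both groups, the qualitative contact before the follow-up DKAS is an unstated possible influence.

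The size is uncertain. The kept-manual illustration gives about 0.5 to 1.5 points on assumed inputs. The interview and FGD illustration gives 0.2 to 2.9 points for an assumed effect of 1 to 5 points per participant, and the true effect may be nil. The order of events rests on the text, because the timeline figures are not shown and exact dates cannot be checked.

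A reader might conclude that the retention survey is uninterpretable or that the main result is affected. Neither follows: access is restricted, the manual risk is disclosed, and the primary comparison ends at end-line. This is a minor, cheap improvement.

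**What to change.** 1. Add two or three items to the existing three-month survey: whether the participant holds any copy, photo or notes of the manual; whether they have used iSupport or other dementia material since end-line; and, if so, how often.
2. Report DKAS retention overall. As a descriptive sensitivity analysis, report it again without those who report re-exposure and, using the ID-linked flag, without interview and FGD participants.
3. In Limitations, name the interviews and FGDs beside the manual as possible influences on the follow-up score.

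The cost is a few questions at a contact already planned, one extra descriptive table and a sentence of text. The restricted subset will be small (in the family group possibly 26 − 15 = 11 after excluding interviewees), self-reported and non-random. Some participants may not admit to keeping a manual they were asked to return. It should therefore carry no formal test.

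Moving the interviews to after the follow-up DKAS is not required. It would lengthen recall of user experience, which matters to a feasibility study.
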